**How will you measure, manipulate and/or analyse the information collected?**

**Measuring the effectiveness of the iSupport program:**

A research assistant, who will be blinded to group assignments, will undertake data analysis and will be supervised by CI [name], a biostatistician. Data will be analysed on an intention-to-treat basis based on group assignments. Descriptive statistics will be applied to summarise data. Binary correlation analysis will be performed to compare group using baseline data. A multivariate mixed effect linear regression model will be

applied to fit linear mixed models to examine the primary and secondary outcomes between groups. As the outcome occurs for each individual with repeated time points, the mixed effect models will capture both fixed effects and random effects within the hierarchical structure of the data. The fixed effects, including group effect, time effect and group x time interaction, will be analogous to the regression coefficients. The random effects represent the estimated variability in the intercept to account for repeated measurements. The model will be adjusted by the baseline measure of outcome variable. The maximum likelihood estimate procedure will be used to compare significant differences in primary and secondary outcomes over time and between groups. Univariate models will be first used, then multivariate modelling will be undertaken by adding variables considered clinically important or statistically significant from the univariate model to adjust for confounding effects between variables. A series of models will be undertaken by adding and subtracting variables, with changes in model fit assessed by log likelihood to choose the final multivariate model. The two-sided test will be performed for all analyses and the level of significance will be set at  $p < 0.05$ . All analyses will be performed using Stata software version 16.1.

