#### **Hypothesis**

**Primary hypotheses:** Compared to those allocated to the usual care group, (1) carers receiving the intervention will report (a) at least a 5-point higher mean score on the mental component of the 12-Item Short-Form Health Survey (SF-12) and (b) an improved mean score on the physical component of SF-12; (2) their care recipients will report an improved mean score on the QoL in Alzheimer's Disease (QOL-AD)-Proxy at 12-months follow-up.

**Secondary hypotheses:** Compared to those allocated to the usual care group, (1) carers in the intervention group will report (a) an improved mean score on the Caregiving Self-Efficacy Scale and (b) an improved mean score on the Quality of Social Support

Scale; (2) their care recipients will report (carers acting as proxy respondents) (a) a reduced mean score on the Revised Memory and Behaviour Problem Checklist and (b) fewer unplanned hospital admissions, less emergency department uses and less use of permanent residential aged care at 12 months; and (3) provision of the intervention will be more cost-effective than existing care.

**Aims** - (1) **Aim 1:** to determine the intervention efficacy; (2) **Aim 2:** to establish the intervention cost-effectiveness; and (3) **Aim 3:** to understand carers' experiences in the program.

**Objectives** - How will investigators achieve the aims of the research project?

**Objective 1:** A multicentre randomised controlled trial (RCT) with carers of PLWD will be conducted to test the primary and secondary hypotheses or the intervention efficacy (Aim 1). The intervention will last 12 months.

**Objective 2:** The cost effectiveness analysis will be undertaken alongside the RCT (Aim 2). The primary outcome will be the incremental cost per quality adjusted life years (QALYs) gained for the intervention compared to usual care.

**Objective 3:** A qualitative descriptive design described by Doyle et al. (2019) will be applied to understand carers' experiences in the program (Aim 3) using data from the virtual carer support group meetings.

**Expected outcomes** - What do the investigators anticipate the outcomes of this research will be?

1. The expected outcomes for carers include improved quality of life (QoL), improved self-efficacy, improved quality of social support and positive learning experience in the program.

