**Participant follow up – how are participants monitored during the study?**

All carers in this study will undertake an online survey at three time points: baseline, 6 months and 12 months. The survey will enable researchers to monitor the effectiveness and cost-effectiveness of the education intervention for carers. Carers will also undertake a monthly 10-minute survey (online or hardcopy) to document the previous month health care services utilisation. Carers in the intervention group will also participate in monthly online carer group meeting for 12 months. The meetings will enable researchers to monitor how carers in the intervention group share their learning experience with peers and support each other.

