**Accounting for potential bias, confounding factors and missing information:**

[name] who does not involve in participants recruitment will randomly assign participants (deidentified) into the intervention group and usual care group. This approach will account for potential bias.

Confounding factors will be controlled through statistical analysis design. In order to control the interference of the confounding factors on the research results and reduce the potential bias, univariate models will be first used, then multivariate modelling will be undertaken by adding variables considered clinically important or statistically significant from the univariate model to adjust for confounding effects between variables. A series of models will be undertaken by adding and subtracting variables, with changes in model fit assessed by log likelihood to choose the final multivariate model.

Data will be analysed on an intention-to-treat basis based on group assignments. For missing information in the data analysis, Mean/Model Imputation will be used to reduce the bias in missing data completely at random.

**Sample size and statistical or power issues** – Make sure the size and profile of the sample to be recruited is adequate to answer the research question – please provide details:

The sample size calculation is based on the primary outcome of the SF-12 mental component for carers and is estimated on the basis of an earlier RCT with similar intervention components for carers (Berwig et al., 2017). In that study, the SF-12 mental component for carers increased significantly by an effect size of 0.57 and standard deviation of 8.63. We assume that the same effect size would be observed in our trial. The estimated sample size would be 66 carers per arm using a 2-sample comparison of means for  $\alpha=0.05$  at 90% of power. The Welch-Satterthwaite t-test is used to calculate the sample size for unequal variances. Assuming an attrition rate of 40%, the estimated sample size would be 184 carers in total or 92 per group. A stata code power was used to calculate the sample size. Our investigation indicates that each industry partner provides care services for more than 500 persons with dementia annually and more than 80% of carers use email to communicate with care staff which will ensure sufficient numbers of carers recruited into the study.

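### A random intercept as the only stated device for repeated measurements pools the 6- and 12-month residual variances, so the standard error at 12 months is right only if they are equal

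*Protocol*

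**What the plan says.** The model is set out in the Protocol under *Measuring the effectiveness of the iSupport program*.

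- Fixed effects: "The fixed effects, including group effect, time effect and group x time interaction, will be analogous to the regression coefficients".
- Random effects: "The random effects represent the estimated variability in the intercept to account for repeated measurements".
- Baseline: "The model will be adjusted by the baseline measure of outcome variable".
- Estimation: "The maximum likelihood estimate procedure will be used to compare significant differences in primary and secondary outcomes over time and between groups".
- Testing: "The two-sided test will be performed for all analyses and the level of significance will be set at" 0.05.

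The visit schedule is under *Participant follow up*: "All carers in this study will undertake an online survey at three time points: baseline, 6 months and 12 months". The primary hypotheses, under *Hypothesis*, are set at 12 months; the statement closes with "QOL-AD)-Proxy at 12-months follow-up".

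The protocol names no random slope, visit-specific residual variance, unstructured covariance or robust standard error. It does not say whether the baseline value is also a response row, or whether the baseline coefficient may differ between visits.

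**The concern.** A random intercept with independent residuals of constant variance implies the same total variance at every modelled visit. With baseline as a covariate and 6 and 12 months as the responses, the model estimates one residual variance from both visits and uses it for the 12-month contrast. If baseline predicts 12 months less well than 6 months, or scores spread out over time, the true residual variance at 12 months is larger than the pooled one. The reported standard error is then too small, the interval too narrow and the p-value too low. This falls on the time point that carries the primary hypotheses.

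If baseline is kept as a response row, the model also forces the three pairwise correlations to be equal. With only two response rows there is a single correlation between them, so that second restriction does not bind.

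**Working it through.** **Plan's own figure.** For effect size 0.57, two-sided alpha 0.05 and 90% power, the noncentral t test gives 89.7% power at 65 per arm and 90.15% at 66. The stated 66 per arm is reproduced. The only standard deviation in the document comes from the same paragraph: "increased significantly by an effect size of 0.57 and standard deviation of 8.63".

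**Inputs.** From the protocol: SD 8.63, 92 per arm, 40% attrition (92 × 0.6 ≈ 55 per arm left at 12 months), visits at 0, 6 and 12 months. Assumed, because the document is silent: the correlations ρ6 and ρ12 of baseline with the 6- and 12-month scores, and the SDs σ6 and σ12.

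**Two-row model** (6 and 12 months as responses, one baseline slope, complete data):

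1. Common slope b = (ρ6σ6 + ρ12σ12) / (2σ0).
2. Residual variance at visit t: v_t = σ_t² − 2bρ_tσ_tσ0 + b²σ0².
3. Variance the model uses: p = (v6 + v12)/2.
4. Reported over true SE at 12 months: r = √(p/v12).
5. Type I error = 2{1 − Φ(1.96 r)}.

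Example with unit SDs and 0.7/0.5:

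- b = 0.6
- v6 = 1 − 0.84 + 0.36 = 0.52
- v12 = 1 − 0.60 + 0.36 = 0.76
- p = 0.64
- r = √(0.64/0.76) = 0.918
- type I error 7.2%

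In SF-12 points with 92 per arm, the model would report 8.63 × √(2 × 0.64/92) = 1.02, where the true value is 8.63 × √(2 × 0.76/92) = 1.11.

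| Assumed ρ6/ρ12 and SDs | v6 | v12 | p | r | Type I error |
|---|---|---|---|---|---|
| 0.60/0.60, equal SDs | 0.64 | 0.64 | 0.64 | 1.000 | 5.0% |
| 0.62/0.58, equal SDs | 0.616 | 0.664 | 0.64 | 0.982 | 5.4% |
| 0.65/0.55, equal SDs | 0.58 | 0.70 | 0.64 | 0.956 | 6.1% |
| 0.70/0.50, equal SDs | 0.52 | 0.76 | 0.64 | 0.918 | 7.2% |
| 0.60/0.60, SD 10 at 12 months, otherwise 8.63 | 47.83 | 64.17 | 56.00 | 0.934 | 6.7% |
| 0.55/0.65, equal SDs | 0.70 | 0.58 | 0.64 | 1.050 | 4.0% |
| 0.60/0.60, SD 7.45 at 12 months (8.63 × 8.63/10) | 47.79 | 35.63 | 41.71 | 1.082 | 3.4% |

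The correlation between 6 and 12 months does not enter these formulas.

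**Simulation.** With 92 per arm, no true effect and 5,000 trials per scenario, the maximum likelihood random-intercept fit rejected in 6.8 to 7.7% of trials without attrition and 6.4 to 8.0% with 40% attrition, over correlations 0.65/0.55 to 0.7/0.5. With SD 10 against 8.63 it rejected in 7.1 to 7.3%. An unstructured covariance with baseline by time gave 4.9 to 5.7% in the same scenarios. A smaller simulation (1,000 trials per cell) gave 7.3% without attrition and 5.9% with it for 0.7/0.5. Its Monte Carlo error is about 0.7 to 1.0 points.

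**Three-row model** (baseline also a response, change from 0 to 12 months by group, equal SDs). Here r = √{(1 − mean correlation)/(1 − ρ12)}.

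- Correlations 0.7 (0–6 months), 0.7 (6–12) and 0.5 (0–12): mean 0.633, r = √(0.367/0.5) = 0.856, type I error 9.3%.
- Correlations 0.65, 0.65 and 0.55: r = 0.923, 7.0%.
- Weaker early correlation (0.5, 0.6 and 0.6): r = 1.041, 4.1%.

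**The case against.** The strongest reply is that the protocol never says the random intercept is the whole covariance model. A random intercept can be combined with visit-specific residual variances or robust standard errors. Residual covariance, a baseline-by-visit term and degrees of freedom are details that a statistical analysis plan often settles, and that plan is not at hand. This stands in part: that the intercept is the only device, and that the baseline slope is common, are inferences from what the text names. But the text does state how repeated measurements will be handled, so this is a chosen method that can be improved and not merely a gap.

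The second reply is that the error is assumed and can run either way. This stands. Nothing in the document shows that correlation decays or that spread grows, and the opposite patterns make the test conservative.

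A reader might go further and infer that the 12-month interval and p-value will be too optimistic. The document does not support that: with equal residual variances the test holds its level, and with 0.62/0.58 the excess is 0.4 points. A reader might also infer that equal correlation over time is forced in any case. That is true only if baseline is a response row, which the text leaves open.

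**Conclusion.** The point holds in conditional form. As written, the validity of the primary 12-month standard error rests on equal residual variances at 6 and 12 months, an assumption that the protocol neither states nor supports.

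Over the assumed patterns in the two-row model, a nominal 5% test has a true level between about 3.4% and about 8%. Weakening correlation or growing spread gives about 6 to 8%; the reverse gives about 3.4 to 4.0%. With baseline as a response row, the decay cases are worse (7.0% and 9.3% in the examples above). These sizes depend on assumed correlations and SDs and on default independent residuals. This is a cheap improvement: the error is modest and of uncertain sign, but it is easily avoided.

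**What to change.** In *Measuring the effectiveness of the iSupport program*:

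- State that 6 and 12 months are the response visits, with visit as a category, and that baseline enters only as a covariate.
- Replace the random intercept with an unstructured residual covariance for the two visits. Cluster-robust standard errors are an acceptable alternative.
- Add baseline by visit to the fixed effects.
- Fit by restricted maximum likelihood with a small-sample degrees-of-freedom correction.

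The cost is a sentence or two of text, one more covariance parameter (three instead of two), one more fixed effect and possibly a slightly wider interval. Data collection and sample size do not change.

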***Randomisation and interventions***

After baseline data collection, carers will be randomly assigned to receive either the iSupport program or the usual care. To ensure the two groups are of equivalent size and conditions, a block randomisation will be used to allocate carers to one of the two treatment groups for each recruitment site. Stratification will also be used in the block randomisation to ensure equivalent distribution of spouse carers versus non-spouse carers and care recipients with mild versus moderate dementia in each treatment group.

**Arm 1–Usual care group:** Carers will receive the usual carer support provided by Dementia Australia or other publicly funded carer support. They will receive a monthly reminder email that directs them to the Dementia Australia website where they can seek support if they wish.

**Arm 2–Intervention group:** The planned interventions are described in the following.

- (1) Managing transitions: In each study site, carers will be assigned to an iSupport program facilitator and encouraged to request individualised support from the facilitator during transition between care settings (i.e. from hospital to home transitional care) and types (i.e. receiving ambulatory geriatric services, or rehabilitation or palliative care at home in addition to usual home care package) of the PLWD.
- (2) Managing dementia progression: Carers are also encouraged to contact the facilitator to discuss changes in PLWD (i.e., signs of deterioration, changed behaviours and complications) and gain advice to access relevant multidisciplinary care services for timely treatment and care. The facilitator will follow the carers until their needs for support have been met.
- (3) Psychoeducation: Carers will select at least 20 out of 30 learning units that are relevant to them from the online iSupport program to learn over the first 6 months of the trial and revisit or learn new units when they feel it is needed in the second 6 months. The expected time spent on learning the online iSupport learning modules

is no more than 12 hours in total. The completion of each unit will be measured through the program design and will be recorded as data for compliance with the intervention. Carers will receive a certificate for each unit they complete, a strategy to motivate them in the program.

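### The covariates in the primary model are chosen from the outcome data, and the factors that constrain allocation (site, spouse status, dementia severity) are not fixed in it

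*Protocol*

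**What the plan says.** Under *Measuring the effectiveness of the iSupport program*, one linear mixed model serves the primary and secondary outcomes. Its named terms are group, time, group by time and a random intercept for repeated measurements. One covariate is fixed: "The model will be adjusted by the baseline measure of outcome variable".

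All further covariates are left to a selection procedure. Univariate models come first, followed by multivariate modelling by "adding variables considered clinically important or statistically significant from the univariate model to adjust for confounding effects between variables". Variables are then added and subtracted, "with changes in model fit assessed by log likelihood to choose the final multivariate model". The same procedure appears under *Accounting for potential bias, confounding factors and missing information*, where it is offered as the means of controlling confounding. Neither place lists the clinically important variables, gives a threshold for entry or removal, or names a separate primary model.

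On allocation, *Randomisation and interventions* blocks within each recruitment site and adds: "Stratification will also be used in the block randomisation to ensure equivalent distribution of spouse carers versus non-spouse carers", and likewise for care recipients with mild versus moderate dementia. *Sampling strategies* repeats the blocking by site with blocks of four. Neither analysis section says that site, spouse status or severity stays in the model.

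**The concern.** Randomisation already removes systematic baseline confounding. Covariates in a randomised comparison serve precision and should be settled before outcomes are seen. Here the set is settled afterwards, by looking at associations with the outcome.

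Three things are at stake:

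- **Pre-specification.** The trial could not show that the adjusted primary estimate was the one it set out to report. Selection can also run separately for the SF-12 mental component, the SF-12 physical component and the QOL-AD-Proxy, so the three primary hypotheses could each be adjusted for different variables.
- **Discretion.** With no variable list and no threshold, several final models are admissible, and each one displays a group effect.
- **Agreement with the design.** Stratified allocation makes the treatment estimate less variable when the strata are prognostic. A model without the strata does not recognise this and reports a standard error that is too large.

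This is a stated method, not detail left for a statistical analysis plan. A later plan with one fixed model would contradict the protocol.

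**Working it through.** **1. The plan's own figure.** Inputs from *Sample size and statistical or power issues*: effect size 0.57, SD 8.63 ("increased significantly by an effect size of 0.57 and standard deviation of 8.63"), 90% power, two-sided alpha 0.05. The difference is 0.57 × 8.63 = 4.92 points. The normal approximation gives n = 2(1.96 + 1.2816)² / 0.57² = 64.7, so 65 per arm. The exact noncentral-t calculation gives 66, which matches "The estimated sample size would be 66 carers per arm using a 2-sample comparison of means". That calculation uses no covariates, so fixing covariates in the model leaves it unchanged. With 92 per group and 40% attrition, 92 × 0.60 = 55.2, or about 110 completers in total.

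**2. Type I error under the rule as written.** Simulated null trials used N = 184, 4 sites × 2 × 2 strata, blocks of four, and covariance analysis of a single follow-up score. Assumed inputs: the baseline explains 30% of outcome variance; the strata explain 0 to 20%; there are ten other candidates, two of them weakly prognostic; there is a univariate screen and likelihood-ratio backward stepping, both at p < 0.05. There were 4,000 runs per setting.

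| Strata share of outcome variance | Baseline only, no strata | Strata fixed | Data-selected | Most favourable of 15 models |
|---|---|---|---|---|
| 0 | 0.052 | 0.051 | 0.050 | 0.081 |
| 0.05 | 0.044 | 0.051 | 0.049 | 0.076 |
| 0.10 | 0.036 | 0.051 | 0.046 | 0.072 |
| 0.20 | 0.024 | 0.054 | 0.054 | 0.066 |

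The 15 models are baseline only (1), each of the 13 candidates added singly (3 stratification factors + 10 others), and all candidates together (1).

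**3. Fewer models, more candidates.** A second simulation (110 completers, 8,000 null trials per setting) gave 0.047 to 0.051 for the single selected model. Reporting the most favourable of only three admissible models gave 0.071, 0.081 and 0.094 with 10, 20 and 30 candidate covariates.

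**4. How often the rule keeps the stratification factors.** In the step 2 simulation:

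| Strata share | Site | Spouse status | Severity |
|---|---|---|---|
| 0.05 | 22% | 38% | 40% |
| 0.10 | 51% | 69% | 68% |
| 0.20 | 87% | 95% | 95% |

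**5. Cost of leaving them all out.** If the strata explain a share R² of the variance left after the baseline score, the equivalent gain in sample size from fixing them is 1/(1 − R²) − 1. At R² = 0.05 this is 1/0.95 − 1 = 5.3%; at R² = 0.10 it is 1/0.90 − 1 = 11.1%. (R² here is a share of residual variance, whereas the tables use shares of total outcome variance.)

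Power at an assumed effect of 0.35 SD (3,000 runs):

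| Strata share | Baseline only | Strata fixed | Data-selected |
|---|---|---|---|
| 0.10 | 0.83 | 0.86 | 0.87 |
| 0.20 | 0.84 | 0.92 | 0.93 |

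**6. Cost of fixing them.** Site 4 − 1 = 3, spouse status 1, severity 1: five degrees of freedom.

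**The case against.** The best defence is that the written rule does little harm to the test. It selects on association with the outcome and on fit, not on the group p-value, and both simulations put type I error near nominal. That stands. A reader might infer that the error rate is uncontrolled, but the documents do not support that. The 7-9% belongs to a different rule, in which the analyst reports whichever model favours treatment.

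The protocol also says that the analyst is blinded to group assignment and supervised by a biostatistician. This limits choice by direction. It does not remove discretion, because coded arms still yield a coefficient and a p-value for each candidate model.

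A reader might take the fit criterion to mean raw log likelihood, which can only improve as variables are added. The text speaks of changes in fit while adding and subtracting variables. The ordinary reading is likelihood-ratio comparison of nested models, which accounts for degrees of freedom. Even so, no threshold is given and the covariates still come from the outcome data.

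On the stratification factors, the clinical-importance route could admit them; they are not excluded, only not guaranteed. Their omission makes the test conservative, so it creates no false-positive risk. The 5-11% compares fixed strata with none at all, which is not the plan's procedure. In the simulated settings, mechanical selection matched the power of the fixed-strata model, partly because it could also pick up the two other prognostic covariates.

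Finally, neither section limits candidates to baseline variables, but both speak of confounding and neither proposes a post-randomisation covariate. An intention to adjust for such variables cannot be read into the text.

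**Conclusion.** The point holds as a pre-specification weakness. The structure of the model and the baseline adjustment are fixed, so it would be wrong to say that the whole model is unknown in advance. What is unknown is the remaining covariate set, which can vary by outcome and need not contain the factors that constrain allocation.

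- **Rule applied mechanically:** type I error of 0.046 to 0.054 across both simulations, effectively nominal.
- **Discretion misused:** about 7-9%, given an assumed choice of the most favourable model.
- **Prognostic strata not selected:** a conservative test (down to 0.024 when they are wholly omitted and explain 20% of outcome variance) and a loss of at most about 5-11% in effective sample size if they explain 5-10% of residual variance.

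The protocol gives no prognostic strengths, so every simulated figure rests on assumed ones. The case for change does not depend on them: the present text leaves the primary adjustment to be settled after the outcomes are seen, and a fixed set removes that at almost no cost.

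**What to change.** Replace the stepping text in both *Accounting for potential bias, confounding factors and missing information* and *Measuring the effectiveness of the iSupport program* with one pre-specified primary model for each scale outcome. Its fixed effects are the baseline value of that outcome, site, spouse versus non-spouse carer, dementia severity stratum, treatment, time and treatment by time, with the random intercept retained. Label any model with further baseline covariates a sensitivity analysis, and state that no post-randomisation variable may be used as a covariate.

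The change is one of wording. The added variables are already needed for randomisation, the cost is about five degrees of freedom, and the stated sample size does not change. Whether to keep the baseline group comparisons is a separate question and need not be settled for this fix.

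### Three co-listed primary outcomes are each tested at two-sided 0.05, with no order, alpha split or rule for primary success, and only SF-12 mental is sized

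*Protocol*

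**What the plan says.** Under the heading Hypothesis, the protocol lists three results as primary:

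- 1(a), for carers: "at least a 5-point higher mean score on the mental component" of the SF-12.
- 1(b), for carers: "an improved mean score on the physical component of SF-12".
- 2, for people with dementia: "their care recipients will report an improved mean score on the QoL in" Alzheimer's Disease proxy scale at 12 months.

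The section Primary measures repeats the list. It enters the SF-12 with both its domains, and QOL-AD-Proxy, and ranks none above another.

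Under Sample size and statistical or power issues: "The sample size calculation is based on the primary outcome of the SF-12 mental component for carers". The inputs are an effect size of 0.57, a standard deviation of 8.63, alpha 0.05 and 90% power, giving 66 carers per arm before attrition. No effect size is given for SF-12 physical or QOL-AD-Proxy.

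Under Measuring the effectiveness of the iSupport program, one mixed-model strategy serves all primary and secondary outcomes, and the decision rule is: "The two-sided test will be performed for all analyses and the level of significance will be set at" p < 0.05.

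**The concern.** With three outcomes of equal primary standing and one level applied to each, the protocol does not say what the trial must show to succeed. The two natural readings have different consequences. If one significant outcome is enough, 5% is not the error rate of the primary claim. If all three are needed, error is controlled, but the stated power does not describe the chance of success. Whichever rule is adopted is credible only if fixed before the data are seen. Left open, a significant result on SF-12 physical or on the proxy scale alone could be presented as a primary success without control across the three.

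There is also a smaller mismatch in 1(a). It speaks of at least 5 points, while the sample size rests on slightly less than 5 and the analysis section describes no test against 5.

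**Working it through.** **The plan's own figure.** A two-sample t-test with d = 0.57, two-sided alpha 0.05, 90% power and 1:1 allocation needs 65.66 per arm, rounded up to 66. Power at 66 per arm is 90.2%. The stated 66 is reproduced, and it belongs to SF-12 mental only.

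**Inputs for the error rate.** Three primary outcomes (Hypothesis; Primary measures), each at two-sided 0.05 (Measuring the effectiveness of the iSupport program). The correlations between outcomes are assumptions, because the protocol gives none.

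**Reading A: any one significant outcome is a primary success.** Under the global null, with independent outcomes:

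- At least one false significant result in either direction: 1 − 0.95³ = 1 − 0.857375 = 0.1426, or 14.3%. For two-sided tests on jointly normal statistics this is the maximum over all correlations (Šidák's inequality). The distribution-free bound is 3 × 0.05 = 15%.
- At least one false claim of benefit, at 0.025 per test: 1 − 0.975³ = 1 − 0.926859 = 0.0731, or 7.3%, against 2.5% for one test. The distribution-free bound is 3 × 0.025 = 7.5%.

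With a common correlation among the three test statistics:

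| Assumed correlation | Either direction | Benefit only |
|---|---|---|
| 0 | 14.3% | 7.3% |
| 0.3 | 13.6% | 6.8% |
| 0.5 | 12.5% | 6.3% |
| 0.9 | 8.4% | 4.2% |

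Even at 0.9 both columns stay above their single-test values of 5% and 2.5%.

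**Reading B: all three must be significant.** There is no inflation. Joint power cannot exceed the power for SF-12 mental, and it cannot be computed from the protocol because no effect is assumed for the other two outcomes.

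**Effect of possible remedies on SF-12 mental.**

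- Testing it first in a fixed sequence leaves its level at 0.05 and its requirement at 66 per arm.
- A Bonferroni split at 0.05/3 = 0.0167 would need 85 completers per arm for 90% power at d = 0.57. With 66 completers, power would be 80.1%.

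**The 5-point wording.** The planning difference is 0.57 × 8.63 = 4.92 points. Without baseline adjustment, the smallest significant difference is t × 8.63 × √(2/n):

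- 66 per arm: 1.978 × 1.502 = 2.97 points.
- 55 per arm (92 × 0.6 = 55.2, the planned number less 40%): 1.982 × 1.646 = 3.26 points.

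A difference of about 4 points would therefore be significant at either size, yet would fall short of 1(a) as worded.

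**The case against.** **The 14.3% overstates the harm.** The primary hypotheses all predict improvement, so a false success needs a false benefit. This stands: for a success claim, 7.3% against 2.5% is the relevant pair, and 14.3% describes false significance in either direction.

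**No section says one outcome suffices.** The hypotheses are joined as a list, and a reader could take all three as required. This stands too, so the inflation is conditional on Reading A. But the protocol does not state the all-three rule either.

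**The power statement is not wrong as written.** A reader might infer that 90% was offered for the whole primary family. It was not: the sample size section ties it to SF-12 mental. That wording may even hint at a lead outcome, but the hypothesis and measures sections give all three equal status.

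**Order and alpha allocation may be left to a statistical analysis plan.** This would answer a silent protocol. Here the protocol itself fixes 0.05 for every analysis, so a later hierarchy would have to qualify that sentence.

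**The 5-point figure may be only an expected effect.** This largely stands. A reader might infer that the trial has about an even chance of failing its own hypothesis, since 4.92 lies so close to 5. That is near-tautological: an estimate exceeds a value close to its expectation about half the time at any sample size. No section makes an observed 5 points a decision rule.

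**Conclusion.** The point holds in conditional form. The protocol lists three primary outcomes, sizes one and tests all at two-sided 0.05 without a rule for primary success. If any one suffices, the chance of a false significant primary result is up to 14.3% in either direction, and the chance of a false claim of benefit is up to about 7.3% instead of 2.5%. Both figures assume that no outcome is truly affected; the maxima are reached at independence (for benefit, among non-negative correlations), and the lower values rest on assumed correlations. If all three must succeed, error is controlled, but the 90% does not cover the joint claim.

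A reader might conclude that the trial carries a flat 14% risk of a false primary success. The documents do not support that, because they do not say that one outcome is enough and because that figure also counts false findings of harm. The 5-point matter is one of wording only.

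**What to change.** In Hypothesis, Primary measures and Measuring the effectiveness of the iSupport program, name SF-12 mental at 12 months as the lead primary outcome, tested at two-sided 0.05. Test the other two at 12 months in a fixed sequence, each at 0.05 only if the one before is significant. The order of SF-12 physical and QOL-AD-Proxy is the sponsor's choice and should be justified before data are seen.

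Reword 1(a) as superiority (a difference greater than zero) and keep 5 points as the reference for clinical size.

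The change is to wording. It adds no carers and takes no power from SF-12 mental. The cost is that a claim on SF-12 physical or QOL-AD-Proxy becomes conditional on SF-12 mental. This matters because quality of life of people with dementia is part of the study's overall aim. Even if the planning effect is right, the gate would stay closed about 10% of the time with 66 completers per arm (power 90.2%) and about 16% with 55 (power 84.2%). A sponsor unwilling to accept this could state an all-three rule, with power worked out for it, or an alpha split, at the sample size cost shown above.
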